**Fig. 4 Fig4:**
[figure not shown]
WHO public health strategy for Palliative Care

### Supervision of the study implementation

A project/policy advisory group (PAG) involving all key stakeholders will be formulated and apprised of the project activities through periodic meetings. The implementation plan will be continuously evolved with the inputs of the PAG. The activities will be periodically supervised and refined over the intervention period.

### Data collection & statistical analysis plan

Data handling will be done with strict confidentiality and proper coding to ensure anonymity. All data including outcome measures will be recorded and stored in an electronic medical record.

#### Quantitative data

A pre-tested semi-structured questionnaire will be used for collecting background information about the study participants and QoL version II will be used to assess the quality of life. The data will be analysed by using the SPSS version 21 (IBM SPSS Statistics for Windows, Version 21.0. Armonk, NY: IBM Corp.). QoL and improvement of symptom score will be taken as the dependent variables while sociodemographic variables (age, gender, education, marital status, mean household income), disease characteristics (primary site of cancer, duration of disease, stage of disease at diagnosis, performance status, comorbidity, symptom assessment, type of treatment received, hospitalisation and health care utilisation) will be taken as independent variables. Categorical and continuous variables will be presented as frequency (percentages) and mean ± SD/median (IQR) respectively. Comparisons between groups will be made using Chi-square test/Fischer test, independent samples Student t-tests and Mann–Whitney U tests for categorical, normally distributed continuous and non-normally distributed continuous variables, respectively. A P-value < 0.05 will be considered statistically significant. Paired t-test or Wilcoxon Test will be applied to measure the difference in mean scores of the study variables (based on the parametric or nonparametric distribution). Linear logistic regression model may be used to determine the predictors of change in mean knowledge scores (pre-training and post-training assessment). If necessary, subgroup analysis will be done.

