#### Training

The project staff along with the identified community health care personnel from the State Health Authorities, Punjab will be trained at the AIIMS Bathinda after taking permission from the concerned authorities. A multidisciplinary team of experts comprising palliative care specialists, community medicine experts, oncologists, medical social workers, nurses, and psychiatrists will impart comprehensive home-based PC training to potential patients and caregivers. Apart from didactic lectures, field-based experiential training will be provided. Pre- and post-training changes in the knowledge and attitude will be assessed using validated tools.

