#### Proposed Outcome of the study

The expected outcomes of the study are tabulated below (Table 1).

**Table 1 Tab1:** Expected outcomes of the study

Primary outcome	- Development of a feasible and sustainable Comprehensive Coordinated Community based Palliative Care model for Cancer Patients
Services	- % Cancer patients who received PC
Workforce capacity building	- Development of a structured training module for community-based PC. - Number of community health workers trained in PC
Monitoring indicators for evaluating impact of the model	- Change in HRQoL using EORTC QLQ-C30 pre and post C3PAC model deployment. (Permission to use the Hindi and Punjabi versions of EORTC QLQ-C30 has been obtained) - Change in symptoms as measured by an adapted symptom assessment scale. - % Cancer patients cared for at their preferred place of care

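### The model named for predictors of knowledge change, a linear logistic regression, contradicts its numeric outcome and should be replaced by linear regression adjusted for the pre-training score

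*Protocol article*

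**What the plan says.** Three places in the protocol article bear on this analysis.

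- **Training (Phase II).** Knowledge and attitude are measured before and after training: "Pre- and post-training changes in the knowledge and attitude will be assessed using validated tools". The instrument, its range and its standard deviation are not given.
- **Quantitative data.** Scores are first handled as numeric: "Paired t-test or Wilcoxon Test will be applied to measure the difference in mean scores of the study variables". The next sentence turns to predictors: "Linear logistic regression model may be used to determine the predictors of change in mean knowledge scores". The significance level for the section is 0.05.
- **Proposed Outcome of the study, Table 1.** Workforce capacity building is represented by a training module and by a count, "Number of community health workers trained in PC". Change in knowledge is not listed.

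No section defines a cut-off, a pass mark or any two-level version of the knowledge score.

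**The concern.** Linear regression models the mean of a numeric outcome. Binary logistic regression models the probability of a two-level outcome. They answer different questions and need different outcome variables, so a name that combines them does not identify an analysis. A change in a knowledge score is numeric and suits the first model. It suits the second only after someone decides which trainees count as improved.

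The stake is the answer to who gains from training. If the logistic half of the name were followed, the cut would have to be chosen at analysis, possibly after the scores had been seen. The result could then depend on that choice, and part of the information in the scores would be discarded.

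**Working it through.** **Step 1: does the model fit the outcome?** The article gives no sample size, effect or power for this analysis, so there is no stated figure to reproduce. The check is a comparison of the text with itself.

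| Element | What the article gives | Type it implies |
|---|---|---|
| Outcome | Change in knowledge score, before to after training | Numeric |
| Test of scores in the same section | Paired t-test or Wilcoxon | Numeric |
| Binary outcome or cut-off | None | – |
| Model name | Linear logistic regression | Part numeric, part binary |

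Everything around the model name treats the score as numeric. Only the word *logistic* points elsewhere, and nothing supports it.

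**Step 2: what would a binary cut cost, if one were used?** Assume a normally distributed score and a predictor effect near zero. If a share q of trainees falls on one side of the cut, the efficiency of the binary analysis relative to the continuous one is

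E(q) = φ(z_q)² / [q(1 − q)],

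where φ is the standard normal density and z_q is the q-quantile.

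- q = 0.5: 0.3989² / 0.25 = 0.637, a loss of 36%.
- q = 0.3: 0.3477² / 0.21 = 0.576, a loss of 42%.
- q = 0.2: 0.2800² / 0.16 = 0.490, a loss of 51%.
- q = 0.1: E = 0.342, a loss of 66%.

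The range of 36% to 51% therefore holds for cuts between the 20th and 80th percentiles. More extreme cuts cost more.

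**Step 3: cross-checks on assumed inputs.** None of these inputs comes from the article except the 0.05 level, which is taken as two-sided.

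- *Two groups of trainees, standardised difference 0.5, power 80%.* Continuous analysis: 2 × (1.96 + 0.8416)² / 0.5² = 62.8, so 63 per group. A median cut turns the difference into 40.1% versus 59.9% and needs 100 per group, a loss of 1 − 63/100 = 37%. A 20/80 cut gives 13.2% versus 26.8% and needs 134 per group, a loss of 1 − 63/134 = 53%.
- *Simulation with 200 trainees, slope 0.2, 1,500 runs.* Power was 81% for linear regression, 61% for logistic regression cut at the median, and 50% cut at the 80th percentile. The information ratios were 0.587 and 0.445, so losses of about 41% and 55%.

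The cross-checks agree with the formula, with slightly larger losses away from a zero effect. If the score is kept numeric, the loss is zero.

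**The case against.** The strongest reply is that this is a slip of one phrase. The disputed name contains the word *linear*, the preceding sentence compares mean scores, and a misprint for linear regression, or for linear or logistic regression, fits the text at least as well as a plan to dichotomise. Under that reading no information is lost. This stands. It removes any claim that the trial will lose a given share of its information, but it does not remove the contradiction in the printed name.

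Some stronger readings are tempting, and the article does not support them:

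- *That a binary analysis is planned.* The wording is permissive (the model may be used), and no cut is stated.
- *That a logistic model must have an arbitrary cut.* This is true of binary logistic regression. An ordinal logistic model needs no single cut.
- *That 36% to 51% of trainees are in effect discarded.* The instrument, its distribution and the number of trainees are not given, so the range describes a hypothetical analysis.
- *That predictors of a change in mean scores is a separate error.* It is loose phrasing. Regression models a conditional mean given individual characteristics.
- *That regression to the mean is built in.* The article does not say that the pre-training score is left out of the model. Once it is included, using the change or the post-training score as the outcome gives identical coefficients for the other predictors.

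The absence of a covariate list or of a rule for clustering is not a fault here either. A condensed article commonly leaves these to the full protocol or analysis plan.

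**Conclusion.** The point holds as a contradiction between a named model and its outcome. The article names a linear logistic regression for a numeric change score, treats scores as numeric in the sentence before, and defines no binary outcome. As printed, the analysis cannot be run as binary logistic regression without an unstated cut.

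The size is conditional. If a binary cut were used, about 36% to 51% of the information would be lost, assuming a roughly normal score, a small effect and a cut between the 20th and 80th percentiles. If linear regression is what is meant, nothing is lost and only the wording is wrong.

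Severity is low. The analysis is optional and secondary, and knowledge change is outside Table 1. The pre-to-post change itself can still be tested by the paired t-test or Wilcoxon test already named, and the quality-of-life and symptom evaluation is not touched. Confidence is high for the naming error. It does not extend to any statement of what the investigators intended.

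**What to change.** Replace the sentence with: *Linear regression of each trainee's post-training knowledge score on the pre-training score plus the trainee characteristics collected will be used to examine predictors of knowledge gain; scores will not be dichotomised.* This names one model, sets the individual trainee as the unit, and adjusts for a baseline that the trial already measures.

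If logistic regression is truly intended, define the binary outcome, state and justify its cut-off, and do so before the data are seen.

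The cost is one sentence. The pre- and post-training scores are already to be collected, and the covariates are limited to whatever is recorded on trainees, so no new data are needed.

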#### Qualitative data

All the interviews will be conducted by the research team members with expertise in qualitative research, and interviews will be conducted in English, Hindi, or Punjabi (depending upon participants preferences) in a quiet and comfortable setting, ensuring privacy. Field notes will be taken during IDIs and FGDs to ensure conformability. The interviews will be tape-recorded, and transcribed verbatim to text, and interviews conducted in Hindi/Punjabi will be translated into English and then back-translated to ensure appropriateness. Should any participant feels emotionally upset during the interview and decides to opt out, interview will be stopped and counselling session will be offered to him or her. Credibility of the data will be ensured by quality checks, where questions will be rephrased and checks will be done during or at the end of the interviews. An IDI guide and FGD guide will be used and context-specific clarifications will be given to avoid interviewer bias and assure reflexivity. The translated data will be checked for quality and confirmed with language experts of the languages and cultures involved. Data will be coded using deductive and inductive coding. Thematic analysis will be used to analyse the transcripts of implementers and beneficiaries using Atlas.ti 8 software. Both the quantitative and qualitative data will be triangulated.

#### Proposed Outcome of the study

The expected outcomes of the study are tabulated below (Table 1).

**Table 1 Tab1:** Expected outcomes of the study

Primary outcome	- Development of a feasible and sustainable Comprehensive Coordinated Community based Palliative Care model for Cancer Patients
Services	- % Cancer patients who received PC
Workforce capacity building	- Development of a structured training module for community-based PC. - Number of community health workers trained in PC
Monitoring indicators for evaluating impact of the model	- Change in HRQoL using EORTC QLQ-C30 pre and post C3PAC model deployment. (Permission to use the Hindi and Punjabi versions of EORTC QLQ-C30 has been obtained) - Change in symptoms as measured by an adapted symptom assessment scale. - % Cancer patients cared for at their preferred place of care

## Discussion

Palliative Care interventions (like C3PaC) are inherently complex in that they are multi-component and multi-professional [26, 27]. To ensure their feasibility and cost-effectiveness; these interventions should be developed and tested systematically in phases starting with defining the components, barriers, and challenges to implementation (Phase I); developing the intervention (phase II) and implementation and assessing the effectiveness of intervention (Phase III) [26, 27].

The quality of PC services can be determined by how they address the unmet needs and to be met, they first need to be identified [28]. Need assessment (as in Phase I), inherent in the WHO definition of PC, helps in understanding the requirements of the target beneficiaries enabling them to maintain or improve the present state of well-being [29, 30]. It allows designing appropriate services to provide the right care to those “who” and “when” they need it. A systematic assessment of the quantum of target beneficiaries, their issues, sociocultural milieu, local means available, and existing barriers is essential to delineate the gaps, maximize resource utilization, and empirically plan and implement services [31].

Accustomed culture, lack of training, community awareness, and investment in PC are some of the biggest barriers to the provision of PC; necessitating addressing these barriers (training component of Phase II) to ensure sustainable PC services [20]. Poverty, lack of social security, and most healthcare expenditure being out of pocket in India, necessitate PC programs to cater to free medications, support children’s education, and alternative source of family livelihood (establishing links with voluntary organizations in Phase II) [32].

Based on the principles of universal health care coverage, this study is planned to provide a continuum of care to cancer patients starting from detection, throughout the cancer trajectory, while receiving cancer-directed treatment and extending to end-of-life care. The research team has prior experience in establishing and functioning palliative care programs both at regional and national levels. Since PC provides the desired results when started early, preferably at the time of diagnosis, our model aims at timely initiation of care and integration of the model into the existing healthcare system, with an emphasis on primary care and community setting. Any public health interventions can be ethically challenged if activities cannot be sustained after the cessation of external funding [33]. A public health approach will be adopted to address sustainability throughout the planning, implementation, and evaluation of C3PaC (Fig. 4) [34, 35]. PC activities will be tagged alongside the existing community healthcare system to ensure ownership and continued program activities even after the cessation of the project [32].

### Sustainability and scalability of the C3PAC model

Though the study area is selected based on purposive and convenient sampling based on the proximity to the study hospital, the results of this study would be applicable to the regions with similar health systems and socio-demographic backgrounds. The results will be disseminated and used for advocacy for comprehensive care for cancer patients at the district, state and national level.For sustainability strengthening of primary health care system will be done for PC and referral indicators (when to refer) will be provided to local HCP.

### Strengths

Current literature is grossly deficient in terms of empirical research on effective and sustainable models of PC delivery in rural LMIC [5, 36]. The meager literature has been criticized for lack of precise transparent methodology, data collection, sampling, data analysis and ethical review [5, 19]. To the best of our understanding and knowledge, this will be the first comprehensive evidence-based model of community based PC in rural North India. Our model is unique in that it aims to (1) meet the unaddressed PC needs in the community (2) facilitate early referral of diagnosed cases to cancer care centers for comprehensive management (3) empower healthcare functionaries working in the community in providing comprehensive home-based PC. The collaborative design and coordinated approach will help caregivers and healthcare professionals in implementing palliative regimens in different sociocultural settings and context. It will help policy makers in informed decision making and help them in understanding the challenges in end of life cancer care.

### Anticipated operational difficulties

The scope of PC extends beyond cancer to other chronic life-limiting illnesses. Such a wide definition of the PC population may be impractical, to begin with especially in resource-limited settings [37]. Loss to follow-up due to death or inability to respond to the outcome measures due to cognitive impairment or declining health is common in longitudinal PC studies [25]. This may lead to inadequate statistical power and will be taken into account while calculating sample size [38]. Though challenging, effort will be made to time outcome measures to balance the loss of data due to attrition while allowing sufficient time for the service model to have its effect [39]. The reason for attrition will be systematically analysed, classified (Attrition due to death illness, or Attrition at random), and recorded [24, 40]. Proxy measures will be recorded for patients unable to report themselves [38, 40].

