#### Key informant interviews

In-depth interviews (IDI)/focus group discussions (FGD) with stakeholders will be conducted to explore the PC needs, barriers and challenges. The interviews will be done using an IDI guide or FGD guide that will be developed in consultation with experts in PC, community medicine, and literature review. About 3 FGDs will be conducted among ASHA workers (tentatively 8 per FGD) and in-depth interviews will be conducted till saturation of data is achieved in other key informant interviews. We will tentatively interview 15–20 patients and their caregivers, 15–20 healthcare providers and 5–7 members of voluntary organizations through purposive and convenience sampling. Adult (18 years or more) patients with diagnosed cancer and their family members involved in patient care will be eligible for the interviews.

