### Phase III (deployment of the intervention and feasibility/impact assessment)

A quasi-experimental (pre-post design) will be adopted where the diagnosed patients in Phase I will be considered as controls. To these identified patients, the C3PaC model will be deployed in the form of an intervention over a period of 12 months. The focus will be to provide home-based PC to cancer patients throughout the cancer trajectory, with referral to a tertiary care center for either cancer-directed treatment or management of difficult-to-manage symptoms. The patient information (e.g. demographics, diagnosis, stage of cancer, treatment details, palliative performance scale; physical, psychosocial, and spiritual needs, follow-up details) will be keyed into an electronic record to enable electronic exchange of information among the team members [22].

After one year of intervention, post-intervention data collection will be done to assess the impact, feasibility, sustainability, and scalability of the model using a mixed-method approach. Validated tools like Quality of Life (QOL) version II and the European Organisation for Research and Treatment of cancer Quality of Life Questionnaire Core 30 (EORTC QLQ-C30) will be used after taking appropriate permissions to assess the impact of the C3PAC model on QOL pre and post-C3PAC model deployment. QoL version II has strategically been chosen as their validated translations in the local language are available and both have been used extensively in PC research; thereby improving the generalisability of the results [23–25].

To explore the feasibility and acceptability of this model, FGD and IDI will be conducted with the key informants (as Phase I). The sustainability of this model will be ensured by using the WHO Public Health Strategy for PC to strengthen health systems (Fig. 4) [1].

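### The attrition classes have no place for withdrawal because of the model or its assessments, so by elimination such losses would be summarised as random

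*Protocol article*

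**What the plan says.** The protocol article deals with attrition under Anticipated operational difficulties. It expects losses of one kind: "Loss to follow-up due to death or inability to respond to the outcome measures due to cognitive impairment or declining health is common" in this field. It then states that "The reason for attrition will be systematically analysed", and that it will be "classified (Attrition due to death illness, or Attrition at random), and recorded". The phrase on death and illness has no separator, so the scheme may have two classes or three. The random class is not defined in the article.

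Three other places bear on the point:

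- Table 1 (Proposed Outcome of the study) gives the primary outcome as "Development of a feasible and sustainable Comprehensive Coordinated Community based Palliative Care model for Cancer Patients". Its indicators cover receipt of palliative care, staff training, quality of life, symptoms and place of care. None is a withdrawal or refusal rate.
- The Phase III section says that "the C3PaC model will be deployed in the form of an intervention over a period of 12 months". The patients identified in Phase I serve as the controls and also receive the model, so there is no parallel group.
- For acceptability, the same section says: "To explore the feasibility and acceptability of this model, FGD and IDI will be conducted with the key informants (as Phase I"). In Phase I (Key informant interviews) the plan is: "We will tentatively interview 15–20 patients and their caregivers", with healthcare providers, voluntary-organisation members and focus groups of community health workers besides. The interviewees are found "through purposive and convenience sampling".

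**The concern.** A list that runs death, illness, random leaves one destination for everything that is neither death nor illness. That remainder can hold a family that moved to another district, which may well be unrelated to the study. It can also hold a patient who refuses further home visits, finds the contact distressing, or tires of the questionnaires. The second kind of loss is caused by the intervention or its measurement, and random is the wrong word for it.

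This matters more here than in many trials. Feasibility is written into the primary outcome, and a pre-post design has no concurrent arm in which excess withdrawal would show. How many people who could have continued chose not to is one of the few direct numerical signs of whether the model is acceptable. The classification as worded does not produce that number.

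**Working it through.** The article states no sample size, attrition rate or withdrawal rate, so there is no figure to reproduce. The check is a reading of the passages, followed by an illustration on assumed numbers.

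**1. Is there a class for model-related withdrawal?** The classes are death, illness and random. Read as two classes or as three, none names burden, distress, dissatisfaction or refusal. The expected causes of loss listed just before (death, cognitive impairment, declining health) do not name them either.

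**2. Where would such a patient be coded?** Not under death and not under illness, so under random. This is an inference by elimination. The article neither defines the random class nor says that refusals belong in it.

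**3. Does the reason survive elsewhere?** Partly. The sentence says that the reason is analysed and recorded as well as classified, so the raw reason should be in the data. Follow-up details also go into the electronic record described under Phase III.

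**4. Do the interviews supply the missing number?** They can supply accounts. Community health workers (about 3 focus groups of roughly 8), 15–20 providers and 5–7 voluntary-organisation members may report refusals, even where the patient has gone. But nothing says that patients who left will be sought, and purposive and convenience samples yield themes, not a rate.

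**5. Does Table 1 report it?** No. The percentage of patients who received palliative care could count someone who received it and then declined it.

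**6. How much can the summary hide?** Assume 100 patients: 40 lost to death or illness, 10 classed as random, 50 completing. Those able to continue number 50 + 10 = 60.

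- If all 10 moved away, model-related withdrawal is 0/60 = 0%.
- If all 10 left because of the model, it is 10/60 = 17%.

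The three-class summary is the same in both cases. Keeping 50 completers and varying the random class:

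| Classed as random | Able to continue | Range of model-related withdrawal |
|---|---|---|
| 5 | 55 | 0% to 5/55 = 9% |
| 10 | 60 | 0% to 10/60 = 17% |
| 15 | 65 | 0% to 15/65 = 23% |

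These counts are assumptions. They show what the classes cannot distinguish and do not predict this study's losses.

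**The case against.** The strongest reply is that the sentence already protects the information: reasons are analysed and recorded, and the classes only summarise them. That stands. A reader might infer that any sign of harm or unacceptability would vanish, or that the study would report a model-related withdrawal rate of zero. The text supports neither, because nothing limits reporting to the three classes.

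A reader might also infer that scores missing in the random class will be treated as ignorable. The article does not say so. It offers labels for recording and links them to no analysis; the handling of missing data may sit in a full protocol or analysis plan that is not shown.

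A third tempting step is to put a bias on the quality-of-life result. Suppose 50 completers gain 5 points and 10 leavers would have lost 10. The mean over all 60 is (50 × 5 − 10 × 10)/60 = +2.5, against +5.0 in completers. The arithmetic is right, but the gap arises because leavers have no post-intervention score. Renaming their class recovers no score and changes no estimate, so this figure cannot be charged to the classification.

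Two further replies carry some weight. Referral to the tertiary centre for symptoms that are hard to control is part of the model, so leaving home care for that reason is not in itself withdrawal. And a full code list normally belongs in the full protocol or case report form. The second reply does not dispose of the point: the article goes beyond omitting detail and states a set of classes, one of which has a misleading label.

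**Conclusion.** The point holds in a limited form. As worded, the classes have no place for withdrawal caused by the model or its assessments, and by elimination those losses would be summarised as random. That is the wrong description of a loss that bears on the feasibility part of the primary outcome. The consequence is a misleading attrition summary and no reported withdrawal rate. It is not the loss of the underlying information, and it supports no statement about ignorable missingness or a corrected quality-of-life estimate.

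The size cannot be given, because the article states no attrition figure; on the assumed counts above, the summary could leave a rate anywhere between 0% and 9% to 23% unresolved. The conclusion rests on reading the classes as exhaustive, which the wording suggests, and on the random class having no narrower definition elsewhere. It is an inexpensive improvement to a stated rule.

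**What to change.** Under Anticipated operational difficulties, drop the random class and list these classes:

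- death;
- illness or cognitive decline;
- withdrawal related to the model or the assessments (burden, distress, dissatisfaction, refusal by patient or family);
- move out of the area or to care outside the model, not counting referral within the model;
- reason unknown.

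No class should be called random in advance. In Table 1, add the model-related withdrawal rate as a feasibility indicator and state its denominator; showing it both for all patients who entered Phase III and for those not lost to death or illness would avoid argument.

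The cost is wording and one coded field, since reasons are already to be recorded. The codes should be set before follow-up begins, because reasons are hard to recover once patients have left. The one downside for the sponsor is that reported feasibility may look less favourable.
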